### Statistical analysis plan

Descriptive findings will be explored regarding numbers recruited, completing, dropping out and summary characteristics of each arm at baseline. CI estimation, not p value, will be used as the appropriate analysis for pilot studies.^74^ For all binary outcomes, we will therefore compute the number and proportion in each arm, and 95% CI.

Exploratory analysis of the treatment effect will be conducted. Intention-to-treat analyses will be conducted with participants as originally allocated at randomisation to avoid bias. Significance levels will be set at <0.05 with two-tailed tests. Effect size for the performance outcomes will be explored using ANCOVA with adjustment for baseline value,^75^ and we will report mean differences in outcomes between arms with 95% CIs. SD of each outcome will be estimated, to inform the power calculation for a definitive trial.

Further exploratory analysis will be piloted to highlight any potential modifications required for the definitive trial. This will include integrating process and outcome data to maximise the interpretation of results.^76^ For example, to address the question of the relationship between LDL-cholesterol and variation in adherence levels to the diet, on-treatment analysis will be used, in which results for participants who adhered to the diet will be compared with results from those allocated to the diet (standard intention-to-treat approach). To address the question regarding differences in responses to the intervention between subgroups of participants, regression analysis will be used in the definitive trial (as the power will be insufficient in the pilot study), with tests for interactions to identify participants most and least likely to benefit from the intervention.

Although this trial is not sufficiently powered to compare outcome between intervention arms, estimates of differences between arms will be compared. In the event that the effect of the intervention is large (in the region of 0.5 mmol/L or 10% difference in LDL-cholesterol reduction between groups at 6 months) this study will have sufficient power and it will be important not to miss such large effect sizes if they exist.

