## Methods and analysis

### Design

This is a two-arm, parallel, multicentre RCT for people with HIV dyslipidaemia. The two arms are:
Diet1—reduced saturated fat;Diet2—Mediterranean Portfolio Diet.

Randomisation will be stratified according to gender and smoking status. The trial is funded by the National Institute for Health Research (NIHR) Doctoral Fellowship Programme and has been registered with the International Standard Randomised Controlled Trial Number registry (identifier: ISRCTN32090191). The study flow chart in figure 1 shows progression through the study for individual participants.

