### Sample size

A CI approach was used to estimate the sample size required to establish feasibility.^48^ The criterion for success is that the definitive trial will be feasible if the attrition rate is <20% (or complete follow-up in at least 80% of all recruited participants). With a sample size of 60 participants, the expected attrition rate of 20% can be estimated with a 20% (95% CI 10% to 30%) margin of error. This upper bound of 30% is appropriate as it is the cut-off used to determine which trials constitute best evidence for behavioural intervention^49^ and which trials qualify to receive funding for implementation by the Centers for Disease Control and Prevention 2010.^50^

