### Allocation strategy

Participants will be randomly allocated to Diet1 or Diet2 in a 1:1 ratio on their second trial visit. A statistician from the University of Birmingham will produce a computer-generated allocation sequence using random block sizes of 2 and 4, stratified by gender and smoking status. Block sizes will be concealed until completion of the trial. The research dietitian will allocate participants according to the diet number concealed in the next sequentially numbered, opaque, sealed envelope, relevant for their gender and smoking status. As this is a complex intervention, it is not possible to blind the participants, nor is it possible to blind the healthcare professionals. The terms Diet1 and Diet2 will be used with the aim of achieving participant blinding to the exact content of the diet and type of foods included, to prevent internet searching of diet titles and potential contamination between groups. The success of the level of blinding achieved will be evaluated using questions on intervention preference and self-belief in success.

### Data to be collected at baseline, month 6 and 12

Sociodemographic data on age, gender, ethnicity and occupational status will be collected. Biomedical data will be collected on weight, height, body mass index, waist circumference, body composition and stool frequency/bowel habit. Weight and body composition will be measured in light clothing, barefoot, on a Class 3 Tanita BC420SMA weighing scale (meets Medical Device Directive and Non-Automatic Weighing Instruments European regulations) (Tanita, Tokyo, Japan). Participants will be asked to abstain from food and drink for 4 h prior to the assessment. Height will be measured to 0.1 cm using stadiometers with the supported stretch stature method. Waist circumference will be measured horizontally at the top of the iliac crest, with a flexible non-stretching Seca tape, to 0.1 cm. Bowel habit will be assessed via self-report, to ascertain any disturbances that may require fibre and fluid intake modification.

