### Outcome measures

The primary outcomes for this study are feasibility and acceptability of trial procedures for recruitment, retention, data completion and the intervention. The protocol will be considered viable for a definitive RCT without modification if the following outcomes are met:
Recruitment rates of at least 50% of eligible patients;Attrition rate of <20% by 6 months;Compliance rate of 60% to trial.

If these outcomes are not met, the protocol will be modified in light of the study's findings.

Recruitment rate will be measured as proportion of eligible patients who are subsequently enrolled. Methods of recruitment will be compared: difference between recruitment rate from systematic methods (screening results) and ad hoc methods (posters, referral by multidisciplinary team). Reasons will be sought for declined participation. Appropriateness of eligibility criteria and their practical application for definitive trial will be explored.

Attrition rate is defined as both discontinuation and loss to follow-up of participants at 6 months. Logistic regression will be conducted to assess whether completion is associated with age, gender or allocation preference. Reasons for discontinuation will be sought from participants. The target of 20% (with precision of 10%) is based on the mean attrition rate from five Portfolio Diet studies (13%) and systematic review evidence (18%),^20^ although attrition has ranged from 25%^24^ to 42%^73^ in other HIV diet studies. Acceptability of the intervention and group allocation will be explored by questionnaire, and assessed by comparing attrition rates between the two groups.

Attendance to appointments, collection of supplied foods and completion of food diaries will be used as indicators of participation and study compliance.

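### The ANCOVA leaves out gender and smoking status, the two stratification factors, so its 95% CIs may be slightly too wide (a minor point, with no bias)

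*Protocol article*

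**What the plan says.** **Randomisation.** Under Design: "Randomisation will be stratified according to gender and smoking status". Allocation strategy adds that a statistician will produce a "computer-generated allocation sequence using random block sizes of 2 and 4, stratified by gender and smoking status", in a 1:1 ratio. That gives four strata.

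**Effect model.** Under Statistical analysis plan, the effect on outcomes will be "explored using ANCOVA with adjustment for baseline value". Mean differences between arms are to be reported with 95% CIs. The baseline value is the only covariate named.

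**Other models.** Process Evaluation describes an ANCOVA on LDL-cholesterol that brings in participants' baseline preference for a diet. Outcome measures describes a logistic regression of completion on age, gender and allocation preference. Neither puts the stratification factors into an outcome model.

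**Status.** The Statistical analysis plan calls the treatment-effect analysis exploratory. Outcome measures makes feasibility and acceptability primary, with criteria on recruitment, attrition and compliance.

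**SD.** The same section states: "SD of each outcome will be estimated, to inform the power calculation for a definitive trial". It does not say whether this is a raw, change or residual SD.

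**The concern.** Blocking within strata forces the arms to be nearly balanced on gender and smoking status. If these factors predict the outcome, that balance removes part of the chance variation in the difference between arms. A model without the factors does not know this. It leaves their variance in the error term, and so reports a standard error larger than the one the design achieves.

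At stake is the width of the intervals. The section itself prefers interval estimation to p values for a pilot, and says a large effect on LDL-cholesterol should not be missed. Needlessly wide intervals work mildly against both aims.

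**Working it through.** **Inputs from the article.** N = 60, 1:1, blocks of 2 and 4 within gender by smoking strata. With the expected 20% attrition, 60 × 0.80 = 48 participants complete.

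**The plan's own figure.** The article gives no figure for the ANCOVA. Its only interval is the one for attrition, and it reproduces: 0.20 ± 1.96 × √(0.20 × 0.80 / 60) = 0.20 ± 0.101, or 9.9% to 30.1%, against the stated 10% to 30%. It does not depend on the ANCOVA, so this point does not touch the sample size.

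**Formula.** Let R² be the share of the variance left after baseline adjustment that gender and smoking explain (not in the article). Adding them multiplies the residual SD, and hence the CI width, by about √(1 − R²).

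| R² (assumed) | CI narrows by 1 − √(1 − R²) | Equivalently, too wide by 1/√(1 − R²) − 1 |
|---|---|---|
| 0.02 | 1.0% | 1.0% |
| 0.05 | 2.5% | 2.6% |
| 0.10 | 5.1% | 5.4% |

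**Degrees of freedom.** At N = 60 the residual df fall from 60 − 3 = 57 to 60 − 5 = 55. At N = 48 they fall from 45 to 43.

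**Simulation.** There were 5,000 runs per setting, with the stated blocking. Assumptions not in the article: 30% in one gender category, 40% smokers, baseline/follow-up correlation 0.6, outcome SD 1 and no true difference. Each cell compares ANCOVA on arm and baseline with the same model plus gender and smoking status.

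| N | R² | Coverage of 95% CI | CI half-width | Ratio of half-widths |
|---|---|---|---|---|
| 60 | 0 | 95.2% vs 95.2% | 0.415 vs 0.416 | 1.00 |
| 60 | 0.05 | 95.7% vs 95.1% | 0.415 vs 0.406 | 1.02 |
| 60 | 0.10 | 96.1% vs 95.1% | 0.416 vs 0.395 | 1.05 |
| 60 | 0.20 | 97.3% vs 95.3% | 0.416 vs 0.373 | 1.12 |
| 60 | 0.30 | 98.0% vs 95.5% | 0.417 vs 0.348 | 1.20 |
| 48 | 0 | 94.7% vs 94.8% | 0.468 vs 0.469 | 1.00 |
| 48 | 0.10 | 96.2% vs 95.4% | 0.468 vs 0.445 | 1.05 |

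Three results follow.

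1. The mean estimated difference is about 0 under both models, so omitting the strata causes no bias.
2. The estimator itself is hardly less precise. At N = 60 and R² = 0.10, its actual standard error over the runs is 0.197 without the strata and 0.196 with them. The design has already delivered the gain, and the baseline-only model does not report it.
3. If the strata are not prognostic, adding them costs almost nothing (0.415 against 0.416). The 94.7% at N = 48 is within simulation error of 95%.

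**The case against.** **The effect is small and in the safe direction.** Coverage is at or above nominal, or within simulation error of it. The R² range is assumed. The article says the trial is not powered to compare arms, and none of its three progression criteria uses the ANCOVA. All of this stands, and it limits the point to a minor one.

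**An article condenses the full plan.** The full plan may list the strata. If so, only the article's wording needs completing. But this is more than silence: the section names the model and its adjustment, and the adjustment named does not reflect the randomisation.

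**A stronger reading concerns the SD.** A reader might infer that a raw SD will go unadjusted into the definitive trial's sample size, and as a bare point estimate. With assumed correlations of 0.5 to 0.7, a raw SD would inflate N by 1/(1 − r²) = 1.33 to 1.96. With about 45 df, a pilot SD falls below the true value 53% of the time. The article does not support this reading, for four reasons:

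- It does not say that the SD is raw. The sentence directly follows the ANCOVA sentence, and an outcome SD reported with the baseline/follow-up correlation is a legitimate input for planning an ANCOVA.
- It does not say that the SD will be used without allowance for its uncertainty. How a later power calculation makes that allowance belongs to the definitive trial.
- The two harms cannot both apply to the same SD. If the raw SD were used, the pilot variance (45 df) would fall below the true residual variance in only 11%, 3% or 0.3% of pilots at r = 0.5, 0.6 or 0.7. The 53% applies only if the residual SD is used, and then the oversizing disappears.
- A one-sided 80% upper limit for the planning SD is one convention among several, so its absence is not a fault.

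**Conclusion.** The mismatch is real: randomisation is stratified by gender and smoking status, and the stated ANCOVA adjusts for the baseline value alone. The consequence is conservative intervals, with neither bias nor invalid inference. They are about 1% to 5% too wide if the two factors explain 2% to 10% of the residual variance, and unchanged if they explain none. They would be about 12% and 20% too wide at 20% and 30%, but nothing in the article suggests values that high. All these sizes rest on assumed R², since the article gives no data on how prognostic the factors are.

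This is a minor, nearly free improvement to an exploratory analysis. The undefined SD is at most something to clarify and is not an error.

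**What to change.** In the Statistical analysis plan section, specify: *ANCOVA of the month-6 (and month-12) outcome on arm, baseline value, gender and smoking status.*

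The cost is a wording change and 2 degrees of freedom. Both variables are already needed for randomisation, so no new data are collected.

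Optional clarification: state that the residual SD of this model, or the outcome SD together with the baseline/follow-up correlation, will be reported with its CI for planning the definitive trial.

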**Trial registration number:**

ISRCTN32090191; Pre-results.

Strengths and limitations of this studyThis is a randomised, multicentred, dietary intervention pilot study in adult HIV centres in the UK, with subjective and objective dietary assessment.The outcome and process evaluation data will inform a large definitive trial.The feasibility study design is not powered to measure effect size.

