### Study objectives

The aim of this study is to assess the feasibility, and pilot the design and delivery of a RCT that will subsequently form the framework for a definitive RCT to evaluate the effectiveness of dietary intervention on CV risk of people with HIV dyslipidaemia. The objectives are:
To obtain reliable estimates for recruitment, retention and study attendance compliance;To explore the appropriateness of the trial procedures, design and duration;To understand how the intervention works in practice and its acceptability from the participants’ perspective;To quantify levels of adherence to the dietary intervention and identify contextual factors associated with variation;To conduct process evaluation to assess fidelity and quality of implementation;To determine estimates of the variability of the outcome measures and markers of CV risk, anthropometric measures and quality of life, including LDL-cholesterol, pulse wave velocity and waist circumference.

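### Sufficient power for a large LDL effect is asserted without an SD and for two effect sizes that differ over most of the eligible LDL range; it holds only if the residual SD is small

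*Protocol article*

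**What the plan says.** The Statistical analysis plan section concedes a general limit: "Although this trial is not sufficiently powered to compare outcome between intervention arms". It then makes an exception for a large effect, "in the region of 0.5 mmol/L or 10% difference in LDL-cholesterol reduction between groups at 6 months) this study will have sufficient power", and adds that an effect of that size ought not to go undetected. The strengths and limitations list carries only the general caveat: "The feasibility study design is not powered to measure effect size".

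No SD, baseline-outcome correlation, analysed number or power percentage accompanies the exception. One of the Study objectives is "To determine estimates of the variability of the outcome measures and markers of CV risk", with LDL-cholesterol named among those measures. The Sample size section derives the 60 participants only from the precision of the attrition estimate.

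On inference, the Statistical analysis plan section first says "CI estimation, not p value, will be used as the appropriate analysis for pilot studies" and, in the next paragraph, "Significance levels will be set at <0.05 with two-tailed tests". Treatment effects are to be estimated by ANCOVA adjusting for baseline, as mean differences with 95% confidence intervals.

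**The concern.** A power statement needs an effect, an SD, an analysed number and a test level. Here the SD is absent and is declared unknown elsewhere, and the effect is given on two scales that agree at only one baseline value. The reader is nevertheless told without condition that power will be sufficient.

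What is at stake is the reading of the exploratory LDL result. Someone who accepts the sentence may take a non-significant difference as evidence against a large effect, although the confidence interval may still contain 0.5 mmol/L. The 0.05 level adds to this, because power has meaning only for a significance test, which the same section otherwise sets aside for a pilot.

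**Working it through.** **Inputs from the protocol article.** 60 participants and 20% expected attrition (Sample size); 1:1 allocation (Allocation strategy); two-tailed 0.05, ANCOVA on baseline, effect of 0.5 mmol/L or 10% (Statistical analysis plan); entry LDL above 3 mmol/L (Participants). **Assumed, because the article gives no figure:** the residual SD, the baseline-outcome correlation, the mean baseline LDL, and 80% as the meaning of sufficient power.

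**1. The one sample-size figure that can be reproduced.** For attrition, 0.20 ± 1.96 × √(0.20 × 0.80 / 60) = 0.20 ± 0.101, that is 9.9% to 30.1%. This matches the stated 10% to 30%, but it says nothing about LDL. The LDL power claim cannot be reproduced, since no SD is given.

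**2. Are the two effects the same?** 0.5 / 0.10 = 5.0 mmol/L, so they agree only at that baseline.

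| Baseline LDL (mmol/L) | 10% equals (mmol/L) | 0.5 mmol/L equals |
|---|---|---|
| 3.0 | 0.30 | 16.7% |
| 3.5 | 0.35 | 14.3% |
| 4.0 | 0.40 | 12.5% |
| 4.5 | 0.45 | 11.1% |
| 5.0 | 0.50 | 10.0% |

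The Portfolio Diet results cited in the Introduction imply baselines of 1.36/0.29 = 4.69, 0.61/0.13 = 4.69 and 0.67/0.14 = 4.79, where 10% is 0.47 to 0.48. The pairing suits those trials. At 3.5 to 4.0 mmol/L the 10% effect is smaller and needs (0.5/0.40)² = 1.56 to (0.5/0.35)² = 2.04 times the sample.

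**3. Largest residual SD that gives 80% power.** Analysed number: 60 × 0.80 = 48, or 24 per arm. Power comes from the noncentral t distribution with noncentrality difference / (SD × √(2/n per arm)). At 80% power the detectable standardised difference is 0.826 with 24 per arm and 0.736 with 30. The limit is SD = difference / standardised difference:

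- 0.5 mmol/L: 0.5/0.826 = 0.605 (0.5/0.736 = 0.68 with no attrition)
- 0.40 mmol/L: 0.40/0.826 = 0.484
- 0.35 mmol/L: 0.35/0.826 = 0.424

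Taking one degree of freedom for the baseline covariate does not change these to two decimals.

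**4. Power with 24 per arm over assumed residual SDs.**

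| Residual SD (mmol/L) | 0.5 mmol/L | 0.40 mmol/L | 0.35 mmol/L |
|---|---|---|---|
| 0.5 | 92% | 77% | 66% |
| 0.6 | 81% | 62% | 51% |
| 0.7 | 68% | 49% | 40% |
| 0.8 | 56% | 40% | 32% |
| 0.9 | 47% | 33% | 26% |

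**5. Effect of ANCOVA.** Residual SD = raw SD × √(1 − r²). All raw SDs and correlations here are assumed.

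- Raw 0.8, r = 0.7: 0.571, giving 84% for 0.5 mmol/L, but 66% for 0.40 and 55% for 0.35.
- Raw 0.8, r = 0.6: 0.64, giving 75% for 0.5 mmol/L.
- Raw 0.9, r = 0.5: 0.779, giving 59% for 0.5 mmol/L.

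**The case against.** The strongest reply is that the claim may well be true. It is limited to a large effect, it is hedged as a region, and ANCOVA reduces the SD that matters. For 0.5 mmol/L, plausible combinations give 80% power or more. This stands: a reader might infer that 60 participants cannot deliver the power claimed, but without an SD the document does not show that. Nor can one say flatly that a 10% difference is unpowered. It would be powered with a residual SD at or below about 0.42 to 0.48, and the 3.5 to 4.0 mmol/L baseline is itself an assumption. The Participants section sets no upper entry limit, and the 5 mmol/L withdrawal rule under Dissemination concerns LDL that rises on study, so it does not cap the mean baseline.

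Two further points stand. The general caveat followed by an exception for a large effect is not in itself a contradiction. And progression, under Outcome measures, rests on recruitment, attrition and compliance. A reader might infer that a null LDL test could stop the definitive trial, but no rule there uses LDL, and unmet criteria lead to modification of the protocol.

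It does not rescue the sentence that an article condenses a fuller protocol. The article makes the power claim itself, without condition, while describing the SD as still to be estimated. Nor does the hedge comfortably cover a difference 20% to 30% smaller than 0.5 mmol/L.

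**Conclusion.** The power statement is unsupported as written, and true only for a small residual SD. Its two effect sizes are interchangeable only near a baseline of 5 mmol/L, and the 10% reading is the more demanding one at lower baselines. The size of the problem is what steps 3 and 4 of the working show: the same design moves from comfortable power to less than an even chance of detecting 0.5 mmol/L across a range of SDs that the document gives no means of narrowing. Those figures rest on 48 analysed participants, a two-sided 5% test, and the assumed SDs and baselines.

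The two sentences on confidence intervals and on the 0.05 level do conflict and need reconciling. Overall severity is minor to moderate: LDL is exploratory here, 95% confidence intervals are to be reported anyway, and neither the sample size nor the progression criteria depend on this claim.

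**What to change.** 1. Delete the clause asserting sufficient power, or replace it with a conditional statement on the mmol/L scale alone. For example: *With 48 participants analysed, a two-sided 5% test has 80% power for a 0.5 mmol/L difference if the baseline-adjusted SD is at most about 0.60 mmol/L; this SD is to be estimated in the pilot.* If the sponsor has a working SD and correlation, give them with the resulting power. Do not add a statement that a 10% difference is not powered.
2. Remove the 0.05 significance sentence, or say which analyses it governs and how that fits with relying on confidence intervals.
3. Say that the LDL result will be interpreted by whether the 95% confidence interval for the adjusted mean difference includes 0.5 mmol/L.

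These are wording changes only, with no added participants, visits or measurements. The price is a less favourable stated power.
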